#### Intervention fidelity

To determine whether the intervention was delivered as planned, participant’s completion of the intervention surveys, and time of completion (whether or not they were completed on time) will be recorded. The coaching participant’s completion of the coaching sessions, the length of the coaching sessions, and topics covered in the coaching sessions will also be recorded to measure intervention fidelity.

### Statistical analyses

#### Intervention effects

Data will be analysed using intention-to-treat principles. Physical activity will be modelled using the using linear mixed models with random intercepts, the fixed effects of group (control, tailoring only, tailoring + video-coaching) and time (baseline, post-intervention, 6-months, 12-months), and a group by time interaction and will adjust for potential confounders including gender, age, education, income, employment, location, marital status and BMI if they are associated with physical activity and time.

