**Methods/Design:**

Participants will be randomly assigned to one of three groups (tailoring + online video-coaching, tailoring-only and wait-list control). The tailoring + video-coaching participants will receive a computer-tailored web-based physical activity intervention (‘My Activity Coach’) with brief coaching sessions with a physical activity expert over an online video calling program (e.g. Skype). The tailoring-only participants will receive the intervention but not the counselling sessions. The primary time point’s for outcome assessment will be immediately post intervention (week 9). The secondary time points will be at 6 and 12 months post-baseline. The primary outcome, physical activity change, will be assessed via the Active Australia Questionnaire (AAQ). Secondary outcome measures include correlates of physical activity (mediators and moderators), quality of life (measured via the SF-12v2), participant satisfaction, engagement (using web-site user statistics) and study retention.

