### Recruitment

Print and internet advertising will be used to recruit participants. Print advertising will include newspaper advertising in newspapers and posters and leaflets promoting the intervention will displayed in sporting clubs, schools, the university and medical centres. The internet advertising will include free posts on community websites, and Google and Facebook advertisements. All advertisements will direct interested individuals to a specific recruitment page that is part of the intervention website where they can find out more information about the study and download the participant information sheet. If they are interested in registering, individuals will be asked for their contact details and to give their consent to participate via an online consent form. A researcher will then call participants via telephone to assess their eligibility. Participants who are eligible will be randomly assigned to one of the three groups and notified of their log-in details and intervention starting date. Participants will be allocated at random using a computer generated sequence. Group assignment will only be disclosed after participants have completed the baseline assessment.

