### Sample size

The sample size needed to detect between group differences in physical activity levels across the primary time points (baseline and post-intervention) through linear mixed models was calculated from the sample size analysis developed by K Lu, X Luo and P Chen, Y [62]. The alpha level was set to ≤0.05 (80% power). The effect size was estimated to be small (.43) based on the findings from a recent meta-analysis looking at the effectiveness of physical activity interventions with a minimal control group [12]. Reviews and meta-analyses have found average attrition levels of web-based physical activity levels to be around 25% [12,13]. Therefore an estimated attrition of 25% was factored into the calculations. The analysis revealed that a sample size of 300, or 100 in each study arm, is required for the current study to detect small effects between group differences in physical activity across the two time points.

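### The primary model treats baseline activity as an outcome with a free mean per arm, which is valid but gives up precision that adjusting for the baseline would recover

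*Protocol article*

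**What the plan says.** All places are in the protocol article.

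- Statistical analyses, Intervention effects: a linear mixed model with random intercepts and "the fixed effects of group (control, tailoring only, tailoring + video-coaching) and time (baseline, post-intervention, 6-months, 12-months), and a group by time interaction". Baseline is one of the outcome times.
- Same section, adjusters: the model "will adjust for potential confounders including gender, age, education, income, employment, location, marital status and BMI if they are associated with physical activity and time". Baseline physical activity is not on the list, and no common baseline mean is imposed.
- Abstract, Methods/Design: "The primary outcome, physical activity change, will be assessed via the Active Australia Questionnaire (AAQ"), with week 9 as the primary time point.
- Sample size: the contrast powered is "between group differences in physical activity levels across the primary time points (baseline and post-intervention) through linear mixed models". The inputs are "The alpha level was set to ≤0.05 (80% power"), an effect size of .43, 25% attrition and 100 per arm. No correlation is given, nor the SD that standardises .43.
- Recruitment: "Group assignment will only be disclosed after participants have completed the baseline assessment".

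**The concern.** With group, time (including baseline) and their interaction all free, each arm has its own baseline mean. The week-9 effect is the interaction, that is, the difference between arms in change from baseline.

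The arms are randomised and participants do not know their group when they complete the baseline questionnaire. Any baseline difference between arms is therefore chance. A difference in change subtracts that chance difference in full, whereas the best weight for it depends on how strongly baseline predicts week 9. When the correlation is modest, subtracting all of it adds noise. The listed adjusters do not recover the loss, because as main effects they do not reduce the variance of a within-person change.

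Precision on the primary outcome is at stake, and it can be had from data the trial already collects. Bias is not at issue.

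**Working it through.** **The plan's own figure.** For one pairwise comparison, two-sided 5%, 80% power and d = 0.43, n per arm = 2(1.96 + 0.84)²/0.43² = 84.9, so 85. Allowing for 25% attrition, 85/0.75 gives 114 per arm (342 in total), or 85 × 1.25 gives 107 (321). A one-sided test gives 67, then 90 or 84. None of these is 100. The stated 100 per arm is matched by a difference in change with r of about 0.56, since 84.9 × 2(1 − 0.558) = 75 completers. It is also matched by a baseline-adjusted analysis with r of about 0.34, since 84.9 × (1 − 0.341²) = 75. The article does not say which was meant.

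**Inputs.** From the article: 100 per arm at baseline, 75 at week 9 after 25% attrition, d = 0.43, alpha 0.05. Assumed: two-sided test, one pairwise contrast, d in week-9 SD units, r varied, and equal SDs at first. The week-9 SD is set to 1.

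**Formulas at equal SDs.**

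- Planned model, including the baselines of dropouts: V₁ = 2[(1 − r²)/75 + (1 − r)²/100]
- Baseline-adjusted: V₂ = 2(1 − r²)/75
- Baseline ignored: V₀ = 2/75 = 0.0267, power 75%
- Power = Φ(0.43/√V − 1.96)

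At r = 0.5, V₁ = 2[0.75/75 + 0.25/100] = 0.0250 and V₂ = 2 × 0.75/75 = 0.0200.

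| r | V₁ | V₂ | Change in variance | Power, planned | Power, adjusted |
|---|---|---|---|---|---|
| 0.3 | 0.0341 | 0.0243 | −29% | 64% | 79% |
| 0.4 | 0.0296 | 0.0224 | −24% | 71% | 82% |
| 0.5 | 0.0250 | 0.0200 | −20% | 78% | 86% |
| 0.6 | 0.0203 | 0.0171 | −16% | 86% | 91% |
| 0.7 | 0.0154 | 0.0136 | −12% | 93% | 96% |

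Power reaches 80% from r of about 0.53 under the planned model and from about 0.34 with adjustment. At r = 0.3 and 0.4 the planned model is less precise than ignoring baseline (V₁ above 0.0267). If everyone who misses week 9 returns at 6 and 12 months, planned power at r = 0.3, 0.4, 0.5 and 0.6 is 65%, 72%, 79% and 87%, which changes little.

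**Unequal SDs.** Only people not meeting the activity guidelines are eligible, so the spread at baseline may be narrower than at week 9. The table gives the true variance of the week-9 contrast with four visits, constant correlation and the same numbers. The planned model and the common-mean model both use a random-intercept covariance. Percentages are changes from the planned model.

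| Baseline SD / week-9 SD | r | Planned variance | Free baseline slope | Common mean, random intercept only |
|---|---|---|---|---|
| 0.75 | 0.3 | 0.0284 | −14.5% | −13.7% |
| 0.75 | 0.5 | 0.0214 | −6.5% | −3.9% |
| 0.75 | 0.7 | 0.0139 | −2.2% | +5.2% |
| 0.6 | 0.3 | 0.0262 | −7.4% | −5.4% |
| 0.6 | 0.5 | 0.0206 | −2.7% | +4.1% |
| 0.6 | 0.7 | 0.0145 | −6.0% | +12.4% |
| 0.5 | 0.3 | 0.0253 | −3.9% | −0.9% |
| 0.5 | 0.5 | 0.0205 | −2.6% | +7.8% |
| 0.5 | 0.7 | 0.0154 | −11.9% | +14.9% |

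A common baseline mean with an unstructured visit covariance gives the same figures as the free slope. With a random intercept only, the model weights baseline by one pooled correlation, which is the wrong weight when the SDs differ.

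**The case against.** The strongest defence is that nothing here is wrong. A group-by-time model with baseline as an outcome is common, valid and unbiased in a randomised trial. It fits a primary outcome defined as change and a sample size built on the baseline to week-9 contrast. The 100 per arm would even agree with such a contrast at r of about 0.56. All of this stands, so the point concerns efficiency only.

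Three stronger readings are tempting, and the document supports none of them.

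- A reader might infer that the trial is underpowered. That needs a correlation the article does not give. At equal SDs the planned model has 86% power at r = 0.6 and 93% at r = 0.7. With the baseline SD at 0.75 of the week-9 SD it has 84% at r = 0.5.
- A reader might take the quoted test-retest kappa of .52 for the activity questionnaire as evidence of a low correlation. Kappa measures agreement on repeat testing; it is not the correlation of activity minutes between baseline and week 9.
- A reader might infer that imposing equal baseline means is always at least as precise. Under the planned random-intercept covariance it is not, as the last column of the second table shows.

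The article may also leave covariance details to a fuller plan. It does, however, commit to the fixed effects and the list of adjusters, and those settle this point.

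**Conclusion.** The point holds as an avoidable loss of precision on the primary outcome. At equal SDs the variance of the week-9 effect would fall by 29%, 20% and 12% at r = 0.3, 0.5 and 0.7. At r = 0.5 this is worth 0.0250/0.0200 = 1.25, or 25% more participants. With a baseline SD of 0.5 to 0.75 of the week-9 SD, the gain is smaller, roughly 2% to 14%. In every case computed, a freely estimated baseline slope was more precise than the planned model.

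The power statement is conditional. At equal SDs, the model decides whether 80% is reached only for r between about 0.34 and 0.53. Below that range neither analysis reaches 80%, and above it both do. The figures assume one pairwise contrast at two-sided 5% without multiplicity adjustment, and 0.43 in week-9 SD units.

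**What to change.** Use either of these as the primary analysis:

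1. Analyse week-9, 6-month and 12-month activity as outcomes, with baseline activity by time as a covariate whose slope is freely estimated.
2. Keep baseline as an outcome, fit one common baseline mean across arms, and use an unstructured visit covariance.

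Do not impose the common mean with the random-intercept covariance alone. Keep the planned model as a sensitivity analysis, and state the assumed baseline to week-9 correlation and the SD behind .43.

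The change takes a line or two of specification and no new data. It relies on allocation staying undisclosed until baseline is complete, which the article already promises. There are two small downsides. Option 1 drops participants with no follow-up; this costs no precision in the calculation above but should be squared with the intention-to-treat statement. Option 2 has more covariance parameters to estimate.

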#### Secondary analyses

The secondary analyses will be conducted using linear effects modelling to determine the effect of group and time on Theory of Planned Behaviour constructs and quality of life. Linear mixed modelling will also be used to compare retention, satisfaction, intervention fidelity and website user statistics between groups. Multiple regression analyses will be conducted to assess Theory of Planned Behaviour concepts including intention, attitude, subjective norm, perceived behavioural control and planning as mediators for physical activity changes. Multiple regression analyses will also be used to asses these Theory of Planned Behaviour concepts as well as demographic variables (age, gender, income, marital status, education and BMI) as moderators for physical activity changes. Descriptive statistics will be used to assess participant satisfaction and fidelity of the video-coaching session.

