### Procedure

Participants will be randomly assigned to one of three groups, tailoring + video-coaching, tailoring-only or wait-list control. All tailoring groups will receive a web-based physical activity intervention named ‘*My Activity Coach*’ that consists of 4 modules of computer-tailored advice. Additionally the tailoring + video-coaching participants will also receive 4 brief coaching sessions with a physical activity expert to discuss the personalised advice they received in the previous module. To control for exposure to additional intervention contacts in the tailoring + video-coaching groups the tailoring-only participants will receive a total of 4 tailored emails to remind them of the tailored advice they received in the previous module, but they will not receive any coaching. Questionnaire data will be collected at baseline, immediately post-intervention at week 9, and 6 and 12 months post baseline (see Figure 1). All questionnaires will be completed through the intervention website, including the waitlist control group (though no tailored content will be available for these participants). Satisfaction with the intervention will only be measured at 9 weeks in intervention group participants. Participant retention, engagement, and feasibility of the coaching sessions will be measured for the intervention participants throughout the intervention. Participants in the wait-list control group will be given the opportunity to participate in the intervention after they have completed the 12-month follow-up questionnaire (see Figure 1). The research has been approved by the Central Queensland University Human Ethics Committee (H13/04-044), and complies to the Helsinki Declaration.

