#### Participant satisfaction

Intervention satisfaction will be assessed for intervention group participants only. Participants’ satisfaction with different parts of the intervention will be assessed by a questionnaire (68 items) that was specifically developed for this study, though based on previous research [61] and will include items on the questions needed to generate the personalised feedback, the tailored advice, website usability, the coaching sessions (for tailoring + video-coaching participants only) and the overall satisfaction with the program. The majority of items are on a 5-point Likert scale where participants are asked to rate their agreement (strongly agree to strongly disagree) to statements about the intervention, for example, ‘the questions were easy to understand’. Four open ended items will also be included in the sections on the tailored advice, website usability, the coaching session and the overall program to provide participants with the opportunity to describe 1) what they liked, 2) what they didn’t like, 3) any recommendations they have to improve the program and 4) if they have any further comments.

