#### Website user statistics

Website user statistics will be collected for each participant. These will be measured by google analytics software, and include number of website visits, average number of pages viewed during a visit, and average visit duration during the 8 week intervention period and during the 12 month post intervention period leading up to the follow up questionnaires.

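### One linear mixed model is named for retention, satisfaction, fidelity and website use, although it does not suit the repeated yes/no outcomes, the visit counts or the single satisfaction score

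*Protocol article*

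**What the plan says.** The protocol article, Secondary analyses, names one method for four kinds of outcome: "Linear mixed modelling will also be used to compare retention, satisfaction, intervention fidelity and website user statistics between groups". It gives no link function, distribution or alternative for any of them. The same section leaves satisfaction with, and fidelity of, the coaching sessions to descriptive statistics.

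Elsewhere the article describes the outcomes as follows.

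- **Satisfaction** (Procedure): "Satisfaction with the intervention will only be measured at 9 weeks in intervention group participants". Under Participant satisfaction, the questionnaire has 68 items, and "The majority of items are on a 5-point Likert scale".
- **Retention** (Procedure): "Participant retention, engagement, and feasibility of the coaching sessions will be measured for the intervention participants throughout the intervention". No scale is given.
- **Fidelity** (Intervention fidelity): for the modules, "completion of the intervention surveys, and time of completion (whether or not they were completed on time) will be recorded". For coaching participants, session completion is also recorded, with "the length of the coaching sessions, and topics covered in the coaching sessions".
- **Website use** (Website user statistics): "number of website visits, average number of pages viewed during a visit, and average visit duration during the 8 week intervention period", and the same measures over the longer period after the intervention.

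The random-intercept form is spelled out only for physical activity, under Intervention effects.

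**The concern.** A Gaussian mixed model with a random intercept assumes a continuous outcome, repeated measurement and the same variance at every time point. Several of these outcomes break one or more of those assumptions. The variance of a yes/no outcome is p(1 − p), so it changes whenever the rate changes, and retention falls over follow-up by its nature. Visit counts collected over 8 weeks and over a much longer later period will not share a variance. A score taken once per participant carries no information on within-person variation.

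The outcomes are secondary, but the Abstract puts engagement, retention and satisfaction beside physical activity in its statement of purpose, and the Background names retention and engagement as the weak point of web-based programmes. Confidence intervals that are too wide at one visit and too narrow at another would distort what the trial reports on them.

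**Working it through.** **Inputs.** From the article (Sample size): 100 per arm, alpha 0.05 (taken as two-sided) and 25% attrition. The retention paths below are assumptions, because the article gives no rate by time point. The model is taken to be random intercept with group by time, as for physical activity; the article does not say so for these outcomes. The article gives no figure of its own to reproduce on this point.

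**1. Repeated yes/no retention.** A random-intercept model has the same total variance at each time. With balanced data, its estimate is close to the mean of the time-specific variances.

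- True SE of a between-arm difference at time t: √(2·p_t(1 − p_t)/100).
- Model SE: √(2·V/100), where V is the mean of p_t(1 − p_t).
- Ratio: R_t = √(V / [p_t(1 − p_t)]).
- Type I error: 2·[1 − Φ(1.96·R_t)].

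For retention of 95%, 80% and 60% in both arms, the variances are 0.0475, 0.16 and 0.24, so V = 0.4475/3 = 0.149. The ratios are √(0.149/0.0475) = 1.77, √(0.149/0.16) = 0.97 and √(0.149/0.24) = 0.79. Type I error is 0.05%, 5.8% and 12.2%.

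Simulation under the null with 100 per arm agrees with the formula:

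| Assumed retention | Model SE / true SE | Type I error, simulated | Type I error, formula |
|---|---|---|---|
| 95 / 80 / 60% | 1.78 / 0.97 / 0.79 | 0.03 / 6.4 / 12.7% | 0.05 / 5.8 / 12.2% |
| 90 / 75 / 55% | 1.39 / 0.96 / 0.84 | 0.8 / 6.3 / 9.6% | 0.6 / 5.8 / 9.9% |
| 75 / 65 / 55% | 1.10 / 0.98 / 0.94 | 3.2 / 5.3 / 6.1% | 3.3 / 5.3 / 6.4% |
| Baseline 100%, then 75 / 65 / 55% (follow-up shown) | 0.93 / 0.83 / 0.81 | 6.6 / 10.4 / 11.3% | 6.5 / 9.4 / 10.9% |

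The error is conservative where retention is high and anti-conservative where it is low. It is small if rates change little. Including baseline, where everyone is present and the variance is zero, makes the follow-up standard errors too small at every visit.

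**2. Single-time comparisons, 100 per arm.** With an ordinary linear comparison, simulated null rejection is 4.97% for a rate of 75%, 4.4% for a rate of 95%, and 5.0% for an overdispersed count (dispersion assumed). The SE ratio is 0.98 to 1.00. It is also 1.00 for 60% against 90%, and 0.99 for a doubled mean count.

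**3. One satisfaction score per participant.** The variance of each score is σ²_intercept + σ²_residual, and nothing in the data separates the two. A trial fit (150 simulated participants, one score each) gave a Hessian that was not positive definite and split the total variance of 0.552 equally, 0.276 and 0.276. The arm contrast depends only on the sum, so the model collapses to two-arm ordinary regression, with SE √(0.552 × 2/75) = 0.121. The mixed-model routine printed 0.114, which, coming from that Hessian, should not be relied on.

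**4. Remaining measures.** Pages per visit, visit duration and session length are continuous. Session measures exist only in the coaching arm, so they allow no comparison between arms.

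**The case against.** The strongest reply is that linear comparisons are robust. With equal arms and one time point, yes/no and count outcomes keep about 5% error, as step 2 shows. The satisfaction model reduces to ordinary regression, and an item-level model over the 68 items would be identifiable. Several measures are continuous and some are repeated, so a mixed model can be fitted to them. The outcomes are secondary, and a condensed article commonly leaves the model for each variable to the analysis plan. A mixed model with a separate variance at each time point would also avoid the error in step 1.

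Most of this stands, and it limits the point. A reader might infer that the models cannot be fitted at all, or that every standard error is wrong; neither follows. The reply does not remove the defect, because the article does more than leave the model open: it names one, and that one is unsuitable for several of the outcomes listed.

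A reader might also take the Procedure section to mean that retention is not recorded in the control arm, so that differential attrition could not be examined. The documents do not support that. The retention sentence contains no word of exclusion, the Measures section sets no limit by arm, and the wait-list group completes every questionnaire on the website. The Background and the Secondary analyses both plan a comparison of retention across groups. The Procedure wording is loose and needs aligning; the data will exist.

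**Conclusion.** The concern holds in limited form: the sentence is wrong as written for part of what it covers.

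- **Repeated yes/no outcomes** (retention, module completion, on-time completion): standard errors by time point are wrong when rates change. At 100 per arm and assumed retention of 95%, 80% and 60%, type I error is about 0.05%, 6% and 13%; at 75%, 65% and 55% it is only about 3%, 5% and 6%. These sizes rest on the assumed rates and on a random-intercept model with common variance.
- **Visit counts**: a poor model over periods of unequal length.
- **Satisfaction**: the random intercept is redundant and unidentified, though the arm contrast itself can be recovered.
- **Continuous measures**: linear modelling is acceptable.

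Sampling precision at 100 per arm is a separate matter and does not measure this defect. The physical activity analysis and the sample size are untouched. Severity: should be fixed, for secondary outcomes only.

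**What to change.** Replace the sentence in Secondary analyses with one model per outcome:

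- **Retention**: questionnaire completed (yes/no) at week 9, 6 months and 12 months, in all three arms; logistic GEE, or risk differences with confidence intervals at each time point.
- **Module completion and on-time completion**: binomial or ordinal logistic regression, in the two intervention arms.
- **Website visits**: negative binomial regression.
- **Pages per visit and visit duration**: linear regression with robust standard errors, or on the log scale.
- **Week-9 satisfaction**: two-arm linear regression, or ordinal regression for single items.
- **Coaching-session measures**: descriptive, in the coaching arm only, as the section already provides.

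In Procedure, reword the retention sentence so that it matches the comparison across groups planned in the Background and in Secondary analyses.

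The cost is one reworded paragraph and one reworded sentence. Standard software suffices, the sample size does not change, and no new data are needed because questionnaires are completed through the website in every arm.
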